## Abstract

**Background:**

Internet-based interventions can be effective in the treatment of depression. However, internet-based interventions for older adults with depression are scarce, and little is known about their feasibility and effectiveness.

**Objective:**

To present the design of 2 studies aiming to assess the feasibility of internet-based cognitive behavioral treatment for older adults with depression. We will assess the feasibility of an online, guided version of the Moodbuster platform among depressed older adults from the general population as well as the feasibility of a blended format (combining integrated face-to-face sessions and internet-based modules) in a specialized mental health care outpatient clinic.

**Methods:**

A single-group, pretest-posttest design will be applied in both settings. The primary outcome of the studies will be feasibility in terms of (1) acceptance and satisfaction (measured with the Client Satisfaction Questionnaire-8), (2) usability (measured with the System Usability Scale), and (3) engagement (measured with the Twente Engagement with eHealth Technologies Scale). Secondary outcomes include (1) the severity of depressive symptoms (measured with the 8-item Patient Health Questionnaire depression scale), (2) participant and therapist experience with the digital technology (measured with qualitative interviews), (3) the working alliance between patients and practitioners (from both perspectives; measured with the Working Alliance Inventory–Short Revised questionnaire), (4) the technical alliance between patients and the platform (measured with the Working Alliance Inventory for Online Interventions–Short Form questionnaire), and (5) uptake, in terms of attempted and completed modules. A total of 30 older adults with mild to moderate depressive symptoms (Geriatric Depression Scale 15 score between 5 and 11) will be recruited from the general population. A total of 15 older adults with moderate to severe depressive symptoms (Geriatric Depression Scale 15 score between 8 and 15) will be recruited from a specialized mental health care outpatient clinic. A mixed methods approach combining quantitative and qualitative analyses will be adopted. Both the primary and secondary outcomes will be further explored with individual semistructured interviews and synthesized descriptively. Descriptive statistics (reported as means and SDs) will be used to examine the primary and secondary outcome measures. Within-group depression severity will be analyzed using a 2-tailed, paired-sample *t* test to investigate differences between time points. The interviews will be recorded and analyzed using thematic analysis.

**Results:**

The studies were funded in October 2019. Recruitment started in September 2022.

**Conclusions:**

The results of these pilot studies will show whether this platform is feasible for use by the older adult population in a blended, guided format in the 2 settings and will represent the first exploration of the size of the effect of Moodbuster in terms of decreased depressive symptoms.

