## Methods

### Study Design

A single-group, pretest-posttest design will be used in both studies. Assessments will be taken at screening (T–1), at baseline (T0), and postintervention (T1). The intervention will last 8 weeks for the group with mild to moderate depressive symptoms from the general population and 16 to 20 weeks for the group with moderate to severe depressive symptoms from the specialized mental health care outpatient clinic. Written informed consent will be obtained from all participants. Figures 1 and 2 show the participant flow for both studies.

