### Participants

#### General Population

Participants with mild to moderate depressive symptoms will be recruited from the general population in the Netherlands. They will be eligible to participate if they (1) are aged at least 55 years, (2) have a Geriatric Depression Scale-15 (GDS-15) score between 5 and 10, (3) are able to work with a computer, and (4) have access to a computer with internet. Candidates will be excluded from the study if they (1) do not have adequate proficiency in the Dutch language or (2) have suicidal thoughts, assessed as having a score of 1 or higher on the 9th item of the Patient Health Questionnaire 9 (PHQ-9) [32]. Having suicidal ideation is considered an exclusion criterion to minimize the risk of an adverse event during the study period.

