#### Specialized Mental Health Care Service

Participants with moderate to severe depressive symptoms will be recruited via a specialized mental health care outpatient clinic (Geestelijk gezondheidszorg [GGZ] inGeest, Amsterdam, the Netherlands). Patients who are in treatment at the clinic will be eligible to participate if they (1) are aged at least 55 years, (2) have a GDS-15 score between 8 and 15, (3) are able to work with a computer, and (4) have access to a computer with internet. Candidates will be excluded from the study if they (1) do not have adequate proficiency in the Dutch language or (2) have suicidal thoughts, assessed as having a score of 1 or higher on the 9th item of the PHQ-9 [32]. Having suicidal ideation is considered an exclusion criterion to minimize the risk of an adverse event during the study period.

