Patients with moderate to severe depressive symptoms will be recruited from the patient population of the specialized mental health care outpatient clinic. For this group, the following steps will be taken: patients who express interest during intake with their therapist will receive an information letter and an informed consent form at the end of the session. Patients who sign the consent form will be assessed by their therapist to confirm they have moderate to severe depressive symptoms (as assessed with the GDS-15 [41]). Once found eligible for participation, they will receive a link to the baseline questionnaires (T0) through Castor EDC. Once the baseline questionnaires are completed, another email will be sent with the login credentials for accessing the platform. The GGZ inGeest therapists will aid participants with logging in on the platform the first time they use it. Participants are strongly advised to change their password upon the first login. Also in this step, the practitioners will assist the participants with becoming familiar with the platform and answer any questions they might have. It will also be communicated that participants should contact their therapist if they feel their symptoms are suddenly deteriorating. Participants will use the platform in a blended format. The therapists will be trained on how to use the platform before the participants start the treatment. After 16 to 20 weeks of participation (depending on the duration of the treatment), the participants will receive another email with a link to another set of questionnaires to acquire posttreatment assessments (T1). After completing the posttreatment assessments, the participants will receive an email to thank them for their participation and ask them if they wish to be informed of the study’s results. After the treatment ends, 5 participants will be invited to participate in individual interviews, which will be conducted face-to-face, through videoconferencing, or by telephone, to evaluate their experience with Moodbuster.

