### Secondary and Other Study Parameters

Descriptive statistics will be also used to assess the working alliance, technical alliance, and the participants’ use of the intervention (ie, uptake). To investigate baseline differences between participants who complete the studies and those who drop out, a 2-tailed, independent-sample *t* test or a Mann-Whitney *U* test will be used. The within-group secondary outcome of depressive severity at posttreatment will be inspected for outliers and a normal distribution. For each group, the change in depression severity pre- and postintervention will be analyzed using a 2-tailed, paired-sample *t* test with a significance level of α<.05. Effect size will be measured using Hedges *g*, and will be interpreted as follows: small (0.2), medium (0.5), and high (0.8) [64].

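### The uncontrolled pre-post change in PHQ-8 is announced as the size of Moodbuster's effect, which a single-group design cannot estimate

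*Protocol article*

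**What the plan says.** - **Design** (Study Design): "A single-group, pretest-posttest design will be used in both studies". Neither study has a comparator. The intervention lasts 8 weeks in the general population and 16 to 20 weeks in the clinic.
- **Entry** (Participants): candidates from the general population must "have a Geriatric Depression Scale-15 (GDS-15) score between 5 and 10". The clinic criterion is a GDS-15 score of 8 to 15.
- **Analysis** (Secondary and Other Study Parameters): PHQ-8 change from T0 to T1 is tested within each group by a two-tailed paired *t* test "with a significance level of α<.05". "Effect size will be measured using Hedges" *g*, and this "will be interpreted as follows: small (0.2), medium (0.5), and high (0.8").
- **Claim** (Abstract, Conclusions): the results "will represent the first exploration of the size of the effect of Moodbuster in terms of decreased depressive symptoms".
- **Limitations** (Strengths and Limitations): the only weakness named is that the sample may be too small.
- **Clinic baseline**: under Specialized Mental Health Care Service, "Patients who are in treatment at the clinic will be eligible to participate". Under Study Procedure, the people approached are "patients who express interest during intake with their therapist".

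**The concern.** An effect of Moodbuster is a contrast between outcomes with it and without it. These studies observe only the first. The planned *g* is a valid summary of how much PHQ-8 scores changed, but the abstract gives it a causal name, and nothing in the limitations tells the reader otherwise. The word exploration signals imprecision. It does not signal that part of the change may have nothing to do with the platform, and a larger sample would not remove that part.

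What is at stake is the conclusion the studies may draw on depressive symptoms. The article describes the work as preceding a main RCT, so a number labelled as the effect of Moodbuster could be misread later as a between-group effect.

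**Working it through.** **1. What the within-group *g* contains.** The document states no effect size, SD or pre-post correlation, so there is no figure to reproduce. Set side by side, its sections give:

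observed change = treatment effect + natural course + regression to the mean + other care

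- Natural course: 8 weeks, or 16 to 20 weeks (Study Design).
- Regression to the mean: possible, because entry requires a GDS-15 score in a set range (Participants).
- Other care: possible in both groups. In the clinic it depends on whether T0 precedes treatment, which the two statements quoted above leave open.
- Treatment: in the clinic this is face-to-face CBT plus online modules (Study Intervention), so even the first term is not the platform alone.

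With one group there is one equation and several unknowns. This suffices for the point; the rest only shows a possible size.

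**2. Size of the regression part, with zero treatment effect and no drift.** Let Z be the standardised GDS-15 at screening, with mean m and variance v among those selected. Let ρ0 and ρ1 be the correlations of GDS-15 with PHQ-8 at T0 and at T1. For jointly normal scores with equal population mean and SD at T0 and T1:

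- mean change in selected participants = (ρ0 − ρ1) × m
- variance at time k in selected participants = 1 − ρk² × (1 − v)
- *g* = (ρ0 − ρ1) × m / √(average of the two variances)

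The entry ranges are those under Participants. All population means, SDs and correlations are assumptions. GDS-15 is rounded and capped at 0 and 15.

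Worked case, general population, assumed mean 3 and SD 3, entry 5 to 10: m = 1.107, v = 0.213. With ρ0 = 0.7 and ρ1 = 0.4, the change is 0.3 × 1.107 = 0.332. The variances are 1 − 0.49 × 0.787 = 0.614 and 1 − 0.16 × 0.787 = 0.874; their average is 0.744, with root 0.863. So *g* = 0.332 / 0.863 = 0.38.

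| Group, entry range | Assumed GDS-15 mean / SD | 0.7 at both times | 0.6 falling to 0.5 | 0.7 falling to 0.4 |
|---|---|---|---|---|
| General, 5–10 | 3 / 3 | 0 | 0.13 | 0.38 |
| General, 5–10 | 6 / 3.5 | 0 | 0.04 | 0.12 |
| Clinic, 8–15 | 6 / 3.5 | 0 | 0.12 | 0.37 |
| Clinic, 8–15 | 8 / 3.5 | 0 | 0.08 | 0.24 |

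A steeper fall, from 0.7 to 0.35, with lower source means gives more: 0.45 in the general population (mean 3, SD 3) and 0.56 in the clinic (mean 5, SD 3). The Hedges factor 1 − 3/(4df − 1), which is 0.974 at n = 30 and 0.945 at n = 15, would lower these values slightly.

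**3. What the paired test would then show.** Take a non-treatment change of 0.3 pooled SD from any source, and an assumed pre-post correlation r of 0.5 to 0.7. On the scale of the SD of differences this is 0.3/√(2(1 − r)), or 0.30 to 0.39. By the noncentral *t* distribution, the probability of a significant improvement is 0.36 to 0.54 at n = 30 and 0.19 to 0.29 at n = 15. A significant result is therefore not evidence that the platform caused the change.

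**The case against.** The authors can fairly say that the claim is modest. The abstract says first exploration, the analysis section speaks of within-group change, PHQ-8 is secondary, and Future Directions leaves clinical effectiveness to a possible RCT. Results also promises reporting under the CONSORT guidance for feasibility studies, with expressions of uncertainty. All of this stands and keeps the point small. It does not cure the wording of the conclusion or the silence on the missing comparator.

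A reader might infer more than the document supports:

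- *That regression to the mean is built in.* Selection uses GDS-15 at T−1, whereas change is measured on PHQ-8 from T0. If GDS-15 predicts both PHQ-8 scores equally well, the artefact is zero, and no figure in the document supports an assumed decay.
- *That it could reach 0.68 in the clinic.* That value arises only by applying a community distribution (mean 3, SD 3) to patients of a specialised outpatient clinic.
- *That g will be used to size the RCT, which would then be too small.* No section says so; only a caution is warranted.
- *That face-to-face contact is a contaminant.* In the clinic study it is part of the blended treatment under test. It matters only if the result is attributed to the platform.
- *That clinic patients are already under treatment at T0.* The eligibility wording may simply mean patients of the clinic; the two statements leave the matter open.
- *That the standardiser of g, or records of antidepressants and time in treatment, are missing.* A condensed article commonly leaves these to the full protocol or analysis plan.

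**Conclusion.** The concern holds as a fault of interpretation. The abstract assigns to the results a meaning that the single-group design cannot give them, and the limitations do not correct it. The planned *g* describes within-group change. How much of that change is regression to the mean cannot be derived from the document: under the main assumed inputs it runs from 0 to about 0.4 in either group, and natural course and other care come on top, unquantified. These figures rest wholly on assumed score distributions and correlations, whereas the conclusion itself rests only on the absence of a comparator. Severity is minor, because acceptance and satisfaction, usability and engagement are unaffected.

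**What to change.** 1. **Abstract, Conclusions:** replace the phrase on the size of the effect with *a first description of within-group change in depressive symptoms, which cannot be attributed to Moodbuster*.
2. **Secondary and Other Study Parameters:** report the mean PHQ-8 change with a 95% CI, and state that *g* and its size labels describe pre-post change, not a treatment effect.
3. **Strengths and Limitations:** add the missing comparator, naming natural course, regression to the mean and concurrent care, and caution that *g* should not be taken as the between-group effect for a later RCT.
4. **Specialized Mental Health Care Service and Study Procedure:** reconcile the two descriptions of when clinic patients enter, so that it is clear whether T0 precedes treatment.

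The cost is a few sentences and one interval per group. No new data are needed; the claim on depressive symptoms becomes more modest.

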**International Registered Report Identifier (IRRID):**

PRR1-10.2196/41445

## Introduction

### Background

Depression is a common mental disorder that is associated with the substantial loss of a person’s well-being and quality of life [1]. Essential components of depression are depressed mood and loss of interest or pleasure in nearly all activities [2]. Depression constitutes a large and rising proportion of global disease [3] and is a major public health problem [4]. Late-life depression is the third leading contributor to the global burden of disease [5]. Late-life depression can be distinguished from adult depression in several ways. First, depressed older adults may show different or less obvious symptoms than their younger counterparts, and cognitive symptoms (eg, disorientation, memory loss, and distractibility) may be particularly prominent [6]. Cognitive impairment may mask the symptoms of late-life depression, as is often seen in vascular disease, Alzheimer dementia, and Parkinson disease [7]. Second, depression in later life is associated with increased risk of physical and psychological disability, decreased quality of life, and increased costs due to higher health care needs in general [7]. Lastly, depressive symptoms in later life increase the distress of family and friends and the burden of informal caregivers, such as spouses or other family members, which often contributes to social isolation of the older adult with depression [8].

Late-life depression is often not recognized or treated [6]. This is unfortunate, because treatment of late-life depression is effective, and decreases not only depressive symptoms [4], but also secondary symptoms, such as pain, general functioning, and health-related quality of life [9,10]. Depending on the diagnosed type of depression and the severity of the impairment, a variety of treatment interventions can be considered for older adults, such as psychoeducation, psychotherapy, and antidepressants [11]. Although antidepressants are effective as a treatment option for older adults [12], they can put them at greater risk for adverse events compared to younger adults with depression because of multiple medical comorbidities and drug-drug interactions, and can contribute to polypharmacy, which increases with aging [13]. Psychotherapies such as problem-solving therapy, cognitive behavioral therapy (CBT), and interpersonal psychotherapy are associated with fewer risks and have benefits equal to antidepressants [13]. CBT is an especially well studied [13,14] and effective type of psychotherapy for depression in later life [15,16]. Unfortunately, only a small proportion of older adults seek psychological treatment [17]. Internet-based interventions can help bridge this treatment gap [18].

### Internet-Based CBT

In recent years, internet-based interventions for the treatment of various common mental disorders, including depression, have been developed and evaluated [19]. These online treatments may overcome barriers that hinder access to face-to-face treatment, such as costs, long waiting lists, limited access to psychological treatment in particular neighborhoods, and the perceived stigma of seeking treatment for a psychiatric disorder [20]. Internet-based CBT (iCBT) provides the same information and teaches similar skills as traditional face-to-face CBT, but does so through the internet with structured materials [21-23]. Additionally, iCBT interventions can be provided in different ways: with therapeutic guidance (ie, guided), without human support related to the therapeutic content (ie, unguided), or in a blended format (ie, integrating online and face-to-face sessions) [24-26]. Ample research has shown that iCBT interventions for depression are effective compared to inactive and active controls. Guided iCBT outperforms unguided interventions, especially among more severely depressed individuals [19,27,28].

Research into internet-based interventions for older depressed adults is scarce, underlining the need for more research to be able to assess the feasibility and effectiveness of these interventions for this specific group. A study by Spek et al [21] measured the effectiveness of an unguided CBT intervention for older adults (aged between 50 and 60 years) and found that it was at least as effective as face-to-face group CBT in reducing symptoms of depression. Furthermore, a randomized controlled trial (RCT) performed by Titov et al [29] supported the use of therapist-guided iCBT as an evidence-based approach to psychological treatment for older adults (aged between 60 and 76 years) with depression. Despite the fact that older adults are generally positive about internet-based interventions [30], there are hardly any digital interventions for the treatment of depression that specifically target older adults, either within the general population or in specialized mental health care outpatient clinics. Also, with the growing number of older adults in our society, there has been a large rise in the number of patients suffering from depression [31]. Furthermore, older adults are not always able to engage with traditional face-to-face interventions, as they might have limited access to health services due to physical health and constraints or due to limited mobility for other reasons, such as a lack of public transport. The need for innovative and effective digital interventions for older adults is thus a public health priority. Lastly, the study by Spek et al [21] recruited participants from the general population and provided the intervention in an unguided format. We therefore plan to evaluate the feasibility of using the intervention in a specialized mental health care outpatient clinic with a blended format and in the general population with a guided format.

### Aim of the Current Studies

The 2 current studies aim to evaluate the feasibility of an online treatment platform (Moodbuster) that targets depressive symptoms in older adults (aged at least 55 years) in 2 settings. The first study will test the feasibility of Moodbuster with an online guided treatment format for older adults with mild to moderate depressive symptoms recruited from the general population. The second study will test the intervention in a blended treatment format by integrating face-to-face and online sessions into one treatment protocol. It will target older adults with moderate to severe depression recruited from a specialized mental health care outpatient clinic. The primary aim of both studies is to evaluate the feasibility of the online platform in terms of (1) acceptance and satisfaction, (2) usability, and (3) engagement. Secondary outcomes include depressive symptom severity, participant experience with digital technologies, technical alliance, working alliance, and uptake.

## Methods

### Study Design

A single-group, pretest-posttest design will be used in both studies. Assessments will be taken at screening (T–1), at baseline (T0), and postintervention (T1). The intervention will last 8 weeks for the group with mild to moderate depressive symptoms from the general population and 16 to 20 weeks for the group with moderate to severe depressive symptoms from the specialized mental health care outpatient clinic. Written informed consent will be obtained from all participants. Figures 1 and 2 show the participant flow for both studies.

